#### Professional learning for teachers

The school champion will complete a 30 min online course prior to programme delivery. This will include modules covering foundational principles of RT and specific safety recommendations to deliver RT to school-aged youth. Following initial completion of the online learning, the school champion will attend a single full-day workshop covering the background/rationale, structure and implementation of the RT4T programme, delivered by members of the research team with relevant expertise in PE, health promotion, exercise physiology and strength and conditioning.

School champions will be asked to attend the professional learning workshop and deliver a compressed training module to other grade 9 and 10 teachers within their schools. The compressed module comprises a train-the-trainer approach that is supported by resources (ie, presentation slides) provided by the research team. Our goal is to enable all interested and eligible teachers to deliver the RT4T programme to maximise the reach of the RT4T programme across the eligible student population.

#### Project officers

The project officers from five local health districts will participate in a full-day training delivered by the research team. The training will be focused on the following: (1) RT4T programme content, (2) strategies to support teachers, (3) project officer roles and responsibilities and (4) how to assess fidelity of the RT4T programme. Following the teacher workshop, schools randomised to the moderate and high support groups will receive external support from project officers. Project officers with relevant qualifications in PE, health promotion, exercise physiology and/or strength and conditioning will observe teachers’ implementation of the RT4T practical sessions, provide ongoing support and address the various barriers to programme implementation.

### Materials and equipment

All participating schools will receive approximately 100 hardcopy exercise cards to use during practical sessions (see figure 1). Schools allocated to the high implementation support group will also receive a basic RT equipment pack. Each equipment pack will include a variety of low cost, versatile exercise equipment (ie, 4x resistance bands set, 4x 3 kg dumbbells, 4x 5 kg weighted bar and 2x pull up bar stand).

### Measures and data collection

Quantitative assessments will be conducted at baseline (T0), 6 months (post intervention; T1) and 18 months (1 year post intervention; T2). Teachers will complete an online survey (T0, T1 and T2). Personal Development, Health, and Physical Education Heads of Department (20%, n=18) and School champions (20%, n=18) will be invited to participate in face to face or virtual interviews (T1 and T2).

### Implementation evaluation

Implementation outcomes are the effects of deliberate actions to deliver new policies, programmes and services.^45 46^

#### Primary implementation outcome

##### Reach

Our primary outcome is reach, operationalised as the proportion of grade 9 and 10 students from the study schools who participate in the RT4T programme. The proportion will be calculated as a percentage of students from grades 9 and 10 who participate in ≥50% of the RT4T practical sessions divided by the total number of students in grades 9 and 10. We will assess reach by collecting teacher logbooks (ie, attendance lists) at T1 and T2. We have used logbooks previously in school-based health promotion trials^47 48^ and achieved high completion rates, high validity and reliability.^49^ A research team member will request that school champions provide a copy of teacher logbooks.

#### Secondary implementation outcomes

##### Representativeness

We will collect representativeness data (ie, School Index of Community Socio-Educational Advantage value, indigenous students (%) and students with language backgrounds other than English (%)) at the school level using the My School website. This information will be reported descriptively.

##### Dose delivered

Dose delivered is the number of RT4T practical and theory lessons delivered to students. Teachers will be asked to record this information in the RT4T teacher handbooks.

##### Fidelity

Project officers will observe approximately two RT4T practical sessions delivered by a teacher per school (moderate and high support arms) (total observations n= ~120). The research team will observe approximately one RT4T practical session from 50% of the schools allocated to the low support arm (total observations n= ~15). Session fidelity will be assessed by completing an observation checklist that describes the RT4T structure and process (eg, did the teacher include a warm-up?) and to what extent they implemented the SAAFE principles (eg, teacher was supportive and promoted positive student interactions, with answer options ranging from 1=‘*strongly disagree*’ to 4=‘*strongly agree*’).

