**Objective:**

To compare the effects of three implementation support models on the reach (primary outcome), dose delivered, fidelity, sustainability, impact and cost of RT4T.

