### Sample size calculation

We aim to recruit 90 secondary schools, with 30 schools assigned to each of the three treatment arms. This will include an estimated 261 classes and n=~7800 students across the three arms of the trial. Based on our previous research in secondary schools, we estimate 20% of schools will not provide usable data for our primary outcome at follow-up. As few studies have tested the effects of implementation strategies on the reach of the school-based physical activity interventions, there is little information to guide power calculations. Therefore, we estimated that the low support group will achieve 12.5% reach, while both the moderate and high support groups will achieve 25% reach (ie, between-group difference of 12.5%). Our power calculation is based on 90% power, type 1 error rate of 0.025 and SD of 12%. For the continuous secondary student effectiveness outcomes, we assumed an intraclass correlation coefficient estimate of 0.2. If 10% of schools provide usable data (~780 students), our study will have 80% power to detect significant small-to-moderate effects between the treatment arms.

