	Perceived barriers (student)	Addresses student motivation using SAAFE principles. Teachers will learn to deliver RT4T using the SAAFE principles.	✔	✔	✔
Implementation process	Planning for implementation	Teachers will complete an action plan template to support implementation of RT4T in their school. The action plan will include: When they are going to train their staff and how. When they are going to get resources to teachers and how. Roles and responsibilities of the school champion and teachers. School champions will complete the action plan during the full-day professional development workshop.	✔	✔	✔
	Project officers	School champions will be connected to a project officer who will provide ongoing support to the school champions after they have attended the workshop. The project officer will: Attend in person meetings with the school champion to gain commitment. Email/phone/visit the school champions. Support teachers via a closed RT4T Facebook group, which is created by the project manager from RT4T. Complete the checklist as part of the project officer handbook, which is developed by the research team. Stay in touch with the project manager from RT4T and provide all the needed details that are requested by the research team (eg, keep track of the support provided and join the weekly 10-min drop in meetings).		✔	✔
	Evaluation and feedback	The project officers will observe approximately two RT4T session per school and provide feedback on the RT4T structure via email. Observations will be conducted using a standardised checklist developed by the research team that assesses aspects of the RT4T session (eg, did the teachers conduct the warm-up?). Project officers will only provide feedback on the RT4T structure via email.		✔	✔

NSW, New South Wales; RT4T, Resistance Training for Teens; SAAFE, Supportive, Active, Autonomous, Fair and Enjoyable; UoN, University of Newcastle.

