### Statistical analysis

Statistical analyses will be conducted by an independent statistical analysis service—Clinical Research Design, Information Technology and Statistical Support from Hunter Medical Research Institute. Analyses of the primary (programme reach) and secondary outcomes will be conducted using logistic mixed models (SAS Institute, Cary, North Carolina, USA) for dichotomous outcomes, and ordinal or linear mixed effects regression models for continuous outcomes. The primary outcome (ie, reach) will be collected at the school level and assessed using t-tests. Alpha levels will be set at p<0.025 for the comparisons of the moderate and high support arms against the low support arm. If the p values for the differences between the moderate and high support arms with the low support arm reach this threshold, the moderate and high support arms will be compared at a 5% significance threshold. For student-level outcomes, statistical analyses will be adjusted for the clustering of effects at the class level, as students from each school are nested in classes. Although clustering at the school level is negligible after adjusting for clustering at the class level, we will test this assumption and adjust our analyses for school-level clustering if required. For teacher-level outcomes, clustering will be accounted for at the school level. Two potential moderators of effects will be explored using interaction terms (ie, socioeconomic status of school and school location). School socioeconomic status will be determined using the Index of Community Socio-Educational Advantage (ICSEA), which will be obtained from the MySchool website.^60^ School ICSEA values are determined using student-level parent occupation and education data, school location (ie, remoteness), and percentage of indigenous student enrolment.

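### Fidelity is scored by project officers in the moderate and high arms and by the research team in the low arm, so assessor type cannot be separated from either contrast with low

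*Protocol article*

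**What the plan says.** The Objective names fidelity among the outcomes on which the support models are compared: "To compare the effects of three implementation support models on the reach (primary outcome), dose delivered, fidelity". The Statistical analysis section applies mixed models to primary and secondary outcomes and adds: "Alpha levels will be set at p<0.025 for the comparisons of the moderate and high support arms against the low support arm". The Abstract also attaches this alpha to the outcomes in general, and nothing exempts fidelity. Moderate and high are compared with each other, at 5%, only if the comparisons with low reach the threshold.

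The Fidelity section divides the observing by arm. Project officers observe about two practical sessions per school in the moderate and high arms, about 120 in total. For the low arm, "The research team will observe approximately one RT4T practical session from 50% of the schools allocated to the low support arm", about 15 in total. The checklist has two parts: structure and process items (for example, whether there was a warm-up), and ratings from 1 to 4 of agreement that the SAAFE principles were followed.

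The Project officers section states that "schools randomised to the moderate and high support groups will receive external support from project officers", and that the officers "will observe teachers’ implementation of the RT4T practical sessions, provide ongoing support and address the various barriers to programme implementation". Table 1 lists the observation itself as a support strategy for those two arms: "The project officers will observe approximately two RT4T session per school and provide feedback on the RT4T structure via email". It also says that the research team developed a standardised checklist. The officers' full-day training includes how to assess fidelity. Blinding is stated for the data analysts only.

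**The concern.** The people who score fidelity in the supported arms are those whose support is being evaluated. A different group scores the low arm, and no school on one side is planned to be seen by the rater type from the other side. If the two rater types differ systematically in how they use the scale, that difference enters the moderate-versus-low and high-versus-low estimates in full.

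This arises from how the data are collected, so an analysis plan cannot repair it afterwards. Fidelity matters to the trial's argument: the Introduction presents variable delivery under the train-and-leave model as a reason for testing added support. A significant fidelity result against low would be read as evidence that support works.

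**Working it through.** **1. The plan's counts.** Sample size calculation: "with 30 schools assigned to each of the three treatment arms".
- Moderate and high: 60 schools × 2 sessions = 120. Matches.
- Low: 30 schools × 50% × 1 session = 15. Matches.

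**2. Assessor by arm.**

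| | Moderate and high | Low |
|---|---|---|
| Project officers | about 120 | 0 |
| Research team | 0 | about 15 |

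The assessor indicator equals the supported-versus-low indicator. A model containing both is not identified for either contrast with low; a model containing only arm estimates support effect plus rater difference. Moderate versus high is free of this, because assessor type and observation schedule are the same in both.

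**3. Illustration of size.** The documents give no SD for the fidelity score and no rater difference, so both are assumed. Take a school-level SD of 0.5 points on the 1–4 scale, 30 supported schools against 15 low schools, no true effect, and a two-sided 0.025 test (critical value 2.241).
- SE = 0.5 × √(1/30 + 1/15) = 0.158.
- Shift 0.2: z = 0.2/0.158 = 1.27; P(Z > 2.241 − 1.27) ≈ 0.16.
- Shift 0.3: z = 0.3/0.158 = 1.90; P(Z > 2.241 − 1.90) ≈ 0.37.

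**4. A second parameterisation.** Step 3 uses one SD for two-session and one-session school means. Relax this by setting the SD of a single session score to 1 and assuming a school ICC of ρ.
- Supported arm: variance of the mean = (ρ + (1 − ρ)/2)/30, which is 0.020 at ρ = 0.2 and 0.025 at ρ = 0.5.
- Low arm: variance of the mean = 1/15 = 0.067.
- SE = 0.294 (ρ = 0.2) or 0.303 (ρ = 0.5).

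Probability of p<0.025 with no true effect:

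| Shift (SD of a session score) | Stated design | Two sessions in all 30 low schools, same assessor split |
|---|---|---|
| 0 | 0.025 | 0.025 |
| 0.25 | 0.08 | 0.13 to 0.16 |
| 0.5 | 0.28 to 0.29 | 0.50 to 0.60 |
| 1.0 | 0.86 to 0.88 | 0.99 to 1.00 |

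The last column shows that more low-arm visits under the same split raise the error rate. The problem is bias, not the small number of low-arm observations.

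**5. What a common-rater comparison could detect.** Suppose the 15 or so research-team visits were spread evenly, about 5 schools per arm, with the same assumed SD of 0.5.
- SE = 0.5 × √(2/5) = 0.32.
- Difference detectable with 80% power at 0.025 ≈ (2.24 + 0.84) × 0.32 ≈ 0.97 points, on a scale only 3 points wide. A t-test would need slightly more.

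**The case against.** The plan has real safeguards. The observers work from a standardised checklist developed by the research team, and that team trains the officers in assessing fidelity. Both make a large rater difference less likely. They do not show that the difference is zero, and without any overlap between rater types the trial cannot estimate it.

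Part of the measure is largely factual. Whether a warm-up took place leaves little room for leniency, and Table 1 limits the officers' feedback to session structure, so coaching and subjective scoring overlap less than one might suppose. This stands: the concern falls mainly on the SAAFE ratings.

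A reader might infer that officers will be lenient, that any advantage for the supported arms would be wholly rater effect, or that the entire fidelity outcome is uninterpretable. The documents support none of these. They give no evidence on the direction of a rater difference, and the research team is not neutral either, since it developed the checklist and trains both champions and officers.

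The unequal number of sessions mainly affects precision and is partly intended, because observation with feedback belongs to the support being tested. Fidelity is also only a secondary outcome.

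**Conclusion.** The concern holds, within limits. Assessor type is completely confounded with moderate versus low and high versus low on fidelity, and a p-value from either test cannot be attributed to support alone. This follows from the stated allocation of observers and needs no numerical assumption.

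The error rates of about 16% to 37% do need assumptions: an SD of 0.5, a shift of 0.2 to 0.3 points, and no true effect. Other plausible inputs move the figure widely, so they are illustrations and not estimates. The exposure is greatest for the SAAFE ratings and smaller for the structure items.

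Moderate versus high is not affected by the assessor split. The primary outcome, reach, comes from teacher logbooks and is untouched. The limitations mention possible poor fidelity and teacher-collected student data, but not this split. The point should be corrected; it does not threaten the trial's main conclusion.

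**What to change.** 1. Exempt fidelity from the p<0.025 tests against low. Report those contrasts descriptively, with the assessor stated and SAAFE and structure items shown separately.
2. Name the assessor split as a limitation.
3. State that moderate versus high on fidelity is tested on its own at 5%. As written, that test depends on the comparisons with low reaching their threshold; if those are dropped and no new rule is given, the remaining test is undefined.
4. Optionally, place some of the 15 or so planned research-team visits in randomly chosen moderate and high schools, so that one rater type scores all three arms, and base any contrast with low on those ratings.

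Items 1 to 3 are changes of wording. Item 4 relocates visits already planned and needs no added staff. The price is that there is no formal fidelity test against low. The optional comparison would be very imprecise (about 5 schools per arm, detectable difference about 1 point under the assumed SD), would leave fewer low-arm visits for description, and would still be unblinded.

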##### Sustainability

We define sustainability as the extent to which the programme is embedded within school practices. It will be assessed in two ways. First, through an interview with the Personal Development, Health, and Physical Education, Head of Department (at T2). Second, school champions will be asked to complete the Provider Report of Sustainment Scale sustainability tool.^50^ The tool is a brief, pragmatic and generalisable three-item measure for front-line service providers. It assesses evidenced-based practice in different settings and has been shown to be a valid measure of sustainability.

##### Implementation determinants

We define implementation determinants as factors believed or empirically shown to influence implementation outcomes.^51^ We will assess the following determinants: culture, acceptability, feasibility, adaptability, compatibility (appropriateness), dose (satisfaction), capability, opportunity and motivation using a teacher survey (~20 min). This survey has not been used previously; however, it is based on a body of literature per different implementation outcomes including (n=number of survey items): participation in muscle strengthening exercise (6)^52^ culture (1),^53^ acceptability (1), feasibility (1), compatibility (appropriateness) (1),^54^ adaptability (3), dose (satisfaction) (2),^55^ capability (4), opportunity (5) and motivation (4).^56^ All school champions will complete the questionnaire and will advise other teachers delivering the programme within their school to do the same. The research team will send reminders for survey completion to all teachers at 6-month and 18-month follow-up.

### Impact evaluation

Student-level outcome data will be collected from a convenience sample of students who provide informed parental consent. We anticipate that 10% of the sample will provide usable data (n~780 students). Fitness testing, participation in muscle strengthening activity and RT skill competency will be assessed using the RT4T app. The tablet version of the app (adapted from the ‘Burn 2 Learn’ programme)^57^ will be used by teachers to assess students’ fitness, student’s participation in muscle strengthening activity and RT skill competency. We will evaluate upper body muscular endurance using the 90° push-up test.^58^ Isometric abdominal muscular endurance will be measured using the plank hold test.^59^ Standing long jump will assess muscular power, 1 min sit to stand will assess lower body muscular endurance and the 10×5 m shuttle run will assess speed and agility. These fitness assessments are integrated into the RT4T programme and conducted by the teachers at the start (week 1) and at the end (week 8) of the 8-week intervention period.

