## Methods

### Experimental design

We will use a hybrid type III implementation–effectiveness trial design^30^ to evaluate the implementation and effectiveness of the RT4T intervention. We aim to recruit 90 secondary schools and randomise them to one of three groups: (1) low, (2) moderate or (3) high implementation support. The low support group will act as a control group (usual practice). This is the professional development model traditionally used by the NSW Department of Education and the delivery model used for RT4T from 2015 to 2020. In Australia, the academic year is separated into four ‘terms’ of 10 weeks duration. Following training, teachers enrolled in our study will deliver the 8-week RT4T intervention within one (or more) of two school terms (ie, within 6 months post-training). This provides teachers with some flexibility regarding the delivery period for RT4T within their academic year.

Regarding the timeline for the evaluation of the intervention, study assessments are undertaken at baseline, 6-month and 18-month follow-up. Teachers will be encouraged to continue delivering the programme after our research has concluded. Our implementation trial is guided by expert recommendations^31^ and is registered with the Australian New Zealand Clinical Trials Registry (ACTRN12622000861752). The design, conduct and reporting will adhere to the Consolidated Standards of Reporting Trials^32^ statement, the Standards for Reporting Implementation Studies^33^ statement and the Template for Intervention Description and Replication checklist.^34^

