### Participants

#### Teachers

One or two teachers from each enrolled school who teach students in grades 9 and 10 will be recruited to act as a ‘school champion’. They will attend a single full-day professional learning workshop delivered by members of the research team with tertiary qualifications in physical education (PE), health promotion, exercise physiology and/or strength and conditioning. School champions will receive curriculum materials and resources at the workshop and will be asked to deliver a separate 2-hour training for other grade 9 and 10 teachers at their schools, who also have the option to implement the programme with their classes. Teachers can deliver the RT4T sessions to their students during usual PE lessons, co-curricular school sport periods or within an elective subject known as Physical Activity and Sports Studies. Professional learning will align with the NSW Educational Standards Authority accreditation process. Lastly, the learning will contribute to teachers’ required annual training hours.^35 36^

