### Blinding and randomisation

After teachers have completed the RT4T workshop, schools will be randomised to one of three implementation support arms. Schools will be stratified by school type, socioeconomic status and location and randomised using a random number producing algorithm by an independent statistical analysis service. Data analysis will be conducted by individuals blinded to group allocation.

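### Student fitness is measured only in classes that take up RT4T after allocation, so between-arm student contrasts are open to selection that differs by arm

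*Protocol article*

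**What the plan says.** All references are to the protocol article.

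- **Allocation** (Blinding and randomisation): "After teachers have completed the RT4T workshop, schools will be randomised to one of three implementation support arms".
- **Delivery** (Experimental design): after training, "teachers enrolled in our study will deliver the 8-week RT4T intervention within one (or more) of two school terms", that is, within six months.
- **Uptake** (Teachers): school champions train other grade 9 and 10 teachers, "who also have the option to implement the programme with their classes". The section on professional learning likewise aims at interested and eligible teachers.
- **Student data** (Impact evaluation): "Student-level outcome data will be collected from a convenience sample of students who provide informed parental consent". The section expects usable data from about 10% of the sample, roughly 780 students. On timing it says "These fitness assessments are integrated into the RT4T programme and conducted by the teachers at the start (week 1) and at the end (week 8"), counted in programme weeks.
- **Primary outcome**: the section on reach defines it thus: "Our primary outcome is reach, operationalised as the proportion of grade 9 and 10 students from the study schools who participate in the RT4T programme". For planning, the Sample size calculation expects that "the low support group will achieve 12.5% reach, while both the moderate and high support groups will achieve 25% reach".
- **Student-level comparison**: the Sample size calculation claims 80% power for small-to-moderate effects between arms, with an ICC of 0.2. The Statistical analysis section names mixed models, adjustment for class clustering (and school clustering if needed) and two exploratory moderators.
- **Limitations**: the strengths-and-limitations box and the Discussion say that internal validity may suffer because a subset of schools supplies student data and teachers collect it.

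**The concern.** Randomising schools makes the arms comparable in all grade 9 and 10 students. It does not make them comparable in the students who end up being tested, because entry to that group follows allocation and depends on something the support is meant to change. If the primary hypothesis is right, supported schools bring in classes that would not have taken part under low support. Those extra classes may differ in fitness or motivation from the ones that would have adopted anyway.

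A difference in week-8 fitness between arms could then reflect who was tested rather than what support did, and a real difference could be hidden. Impact is a named objective, and the cost-consequence scorecard draws on the secondary outcomes, so such an artefact could reach decision-makers as an effect of support.

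**Working it through.** **1. The plan's own figure.** "Our power calculation is based on 90% power, type 1 error rate of 0.025 and SD of 12" per cent, for a difference of 25 − 12.5 = 12.5 points. Two-sided, by the normal approximation:

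n = 2 × (2.241 + 1.282)² × (12/12.5)² = 22.9, so 23 schools per arm.

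By the t distribution, 24 evaluable schools per arm give 89.8% power. With 20% of schools lost, 24/0.8 = 30 per arm, which matches the plan. The twofold contrast in reach is therefore the planning basis, and the primary calculation stands.

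**2. Who can be measured.** The sequence is workshop, randomisation, a teacher's decision to deliver, parental consent, week-1 test, week-8 test. A class that does not take up RT4T has no week 1 or week 8, and no other route to fitness data in trial schools is described. When consent is sought is not stated; entry after allocation is inferred from testing inside a programme that is delivered after allocation. The Sample size calculation puts the usable 10% in terms of schools (9 of 90, about 3 per arm if spread evenly), while Impact evaluation puts it in terms of the sample. The selection question arises on either reading.

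**3. Illustrative size, selection of individual students.** Assume that entrants are the top fraction p of a standard normal propensity, with p equal to the planned reach. The mean propensity of entrants is φ(z_p)/p:

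- p = 0.125: 1.647
- p = 0.25: 1.271
- difference, low minus supported: 0.376

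Multiply by an assumed correlation between propensity and fitness:

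- 0.3: 0.11 SD
- 0.5: 0.19 SD

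**4. Illustrative size, selection of whole classes.** Only the between-class part of the variance is then in play. With the plan's ICC of 0.2, 0.376 × √0.2 = 0.168:

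- × 0.3 = 0.05 SD
- × 0.5 = 0.08 SD

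**5. Comparison with the detectable effect.** The plan gives no numerical effect size and no number of measured students per class, so its 80% power cannot be reproduced. Assume an equal split (260 students per arm), alpha 0.025, and m measured students per class. The minimum detectable effect is (2.241 + 0.842) × √(2 × DE/260), with DE = 1 + (m − 1) × 0.2:

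| m | DE | Detectable effect (SD) |
|---|---|---|
| 3 | 1.4 | 0.32 |
| 10 | 2.8 | 0.45 |
| 29.9 (7800/261, whole class) | 6.78 | 0.70 |

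The illustrative bias is thus between 0.05/0.70 = 7% and 0.19/0.32 = 59% of the detectable effect.

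**6. What the week-1 value can do.** Suppose selection acts only through week-1 fitness, with the correlations of step 3 and an assumed week-1 to week-8 correlation r of 0.5 to 0.8. The bias, low minus supported, is:

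- week-8 value alone (0.376 × correlation × r): 0.06 to 0.15 SD
- change score (0.376 × correlation × (r − 1)): −0.02 to −0.09 SD
- model conditioning on week 1: 0

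If selection acts through motivation or another unmeasured trait, conditioning on week 1 does not remove it.

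**The case against.** **Covariates.** A reader might infer that the week-1 value will not be used. The article does not say so. The Statistical analysis section lists no fixed effects for the student models, a linear mixed model can carry both test occasions, and covariate lists commonly sit in an analysis plan that is not shown. Silence on week 1 is not a finding.

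**Disclosure.** A reader might infer that the limitations ignore how students come to be measured. They do not: the article calls the sample a convenience sample and admits weaker internal validity because only a subset of schools contributes. What they leave out is that entry may differ by arm.

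**Size and direction.** A reader might infer a bias of 0.11 to 0.19 SD against the supported arms. That needs selection of individual students on motivation. The documents place the choice to deliver mainly with teachers and whole classes, often in usual PE or school sport; only consent and the elective subject bring in students or families directly. Moreover, 12.5% and 25% are planned reach (attendance at half or more of the practical sessions), not the fraction entering the fitness sample. No figure in the documents fixes the size or the sign.

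**Status of the claim.** The article makes no explicit causal claim for the student contrasts, and they are secondary. This stands. Even so, it powers an effect between arms in a randomised trial, and without a caveat readers will take the contrast as randomised.

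**Conclusion.** The point holds for the secondary student outcomes. Entry to the fitness sample depends on uptake after allocation, and uptake drives the outcome that the trial expects to differ twofold. The planned arm contrasts therefore lack the protection of randomisation, and the stated limitations do not say so.

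The size and direction are unknown. The illustration gives about 0.05 to 0.08 SD for class-level selection and 0.11 to 0.19 SD for individual selection. Both rest on assumed correlations of 0.3 to 0.5, a normal propensity, and planned reach standing in for the entry fraction. The upper end would matter against a small-to-moderate target; the lower end would matter less.

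It would go too far to conclude that the primary result is affected. Reach is computed over all grade 9 and 10 students in the study schools, not over those tested.

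**What to change.** In Impact evaluation and Statistical analysis:

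1. State that between-arm student-level results are exploratory, non-randomised comparisons among adopting classes.
2. Base them on models that condition on the week-1 value of the same measure and on the stratification factors (school type, socioeconomic status, location). Say that this does not remove selection on unmeasured traits such as motivation.
3. Report, by arm, the numbers of eligible, consenting and measured students, the numbers of classes and schools they come from, and their week-1 values.
4. Add selection that differs by arm to the limitations.
5. Present week-1 to week-8 change within each arm descriptively only. It has no untreated comparator, is open to maturation and learning effects, and is measured by the delivering teachers, so it should not become the main student result.

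The cost is mainly wording and a participant-flow table; the week-1 tests are already planned. Counts of eligible and consenting students must be kept by school. The price is a weaker claim about student effectiveness by arm.
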